#### Stress test based on heart rate variability data

Previous studies have shown that heart rate variability (HRV) is the most reliable indicator of stress [73, 74]. In the current study, HRV is measured using a wrist wearable sensor equipped with the Philips Cardio and Motion Monitoring Module (CM3-Generation-3, Wearable Sensing Technologies, Philips, Netherlands) which is an integrated module equipped with a photoplethysmographic (PPG) and an accelerometer sensor. Briefly, the wearable is mounted on a participant’s wrist and heart rate is recorded for five minutes in a resting state. After five minutes, the wearable is unmounted and the recorded data is extracted and used for HRV analysis. Compared to on-site clinical monitoring, wrist wearables are efficient, cost-effective, non-invasive, user-friendly, and have been previously validated [75].

### Data management, monitoring and safety

All study materials have been drafted to ensure accurate data collection. All data collected by the research team using paper questionnaires will be kept in locked cabinets at the Erasmus University College (EUC). Data collected from the BeHealthyR website will be downloaded by SS. For confidentiality purposes, all data will be anonymized by the means of an identification number and will be housed on the EUR document vault, a secure digital environment which acts compliant to the General Data Protection Regulation (GDPR). Data backup will be made regularly to ensure data security. Only SS and AS will have access to the collected data. All data will be kept for 10 years after the completion of the study as suggested by the Medical Ethic Review Committee (METC) of the Erasmus Medical University (EMC). Because of the low-risk nature of the BeHealthyR intervention, no adverse events are expected. Therefore, no Data Monitoring and Ethics Committee (DMEC) and interim analyses are required. In case of adverse event, participant complaints or a breach of confidentiality, AS will report the events to the METC according to the ethical guidelines.

### Statistical analysis

#### Sample size calculations

Sample size calculations are based on the primary outcome measures (stress, smoking, and perceived health). To the best of our knowledge, no previous studies have evaluated a similar intervention in low-SES groups. Therefore, it is challenging to determine a prior the necessary sample size for multicomponent behavioral interventions. Previous studies that have evaluated similar components on other outcome measures recommend to aim for a sample size of 20-500 participants per intervention condition with an alpha error of 0.05 and a power of 0.80. to detect the expected effect. Assuming expected attrition of 10%, an initial sample of 300 participants are needed, thus 150 in each intervention condition. All power calculations are done using G*Power [76].

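### The 300 participants said to be needed at 0.80 power do not follow from the printed basis, a range of 20 to 500 per condition plus 10% attrition

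*Protocol article*

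**What the plan says.** Under Sample size calculations, the protocol article ties the sample size to stress, smoking and perceived health, and admits that the size is hard to fix in advance. It then turns to earlier research, which is said to "recommend to aim for a sample size of 20-500 participants per intervention condition with an alpha error of 0.05 and a power of 0.80". By the article's own account, that research looked at related components but at different outcomes, and the effect it was meant to find is given no value. The result follows at once: "Assuming expected attrition of 10%, an initial sample of 300 participants are needed, thus 150 in each intervention condition". G*Power is named as the software. No effect size, standard deviation, event rate or test is printed.

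Three other sections bear on this:

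- Study design gives three arms (SM, SM-B and control) and 300 participants in total.
- Randomization and blinding gives a 1:1:2 ratio, with randomization at group level.
- Data analysis plans logistic regression for two-category outcomes, including high against low stress, and multinomial regression for outcomes with more categories.

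**The concern.** The section is the article's only justification of trial size. Its sole quantitative inputs are a 25-fold range (500/20 = 25), taken from studies of different outcomes, and an attrition rate. A range that wide contains almost any trial size and so selects none. Yet the text moves straight to a single number and calls it needed.

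A reader will take 300 as giving 80% power on the named outcomes. If the trial is null, that reader will treat the result as evidence against effects that the design may have had little chance of detecting. The allocation adds to the problem. The 150 per intervention condition fits two equal groups, not one intervention arm of a three-arm 1:1:2 trial.

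**Working it through.** **Inputs.** From Sample size calculations: alpha 0.05, power 0.80, 20 to 500 per condition, attrition 10%, total 300, 150 per intervention condition. From Randomization and blinding: 1:1:2. Assumptions of this check: two-sided test, two-sample comparison of means with equal variance, independent participants, and the control condition holding the double share (the text does not say which arm does).

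**Step 1: the plan's own figure.** The attrition step closes backwards: 300 × 0.9 = 270 and 150 × 0.9 = 135, so 135/0.9 = 150. The figure of 135 completers per side is not printed and is not an end of the range.

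**Step 2: what the range implies.** Total = (number of shares × n)/0.9, rounded up. For 1:1:2, n is the size of the smaller arms, which gives four shares.

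| Layout | n = 20 | n = 500 |
|---|---|---|
| Two groups | 40/0.9 → 45 | 1000/0.9 → 1112 |
| Three equal arms | 60/0.9 → 67 | 1500/0.9 → 1667 |
| 1:1:2 | 80/0.9 → 89 | 2000/0.9 → 2223 |

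Inflating by 1.1 instead of dividing by 0.9 gives 44 to 1100, about 66 to 1650, and 88 to 2200. Neither end gives 300 under any layout or inflation rule.

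**Step 3: the effect that 300 would match.** For 80% power, d = (1.960 + 0.842) × √(1/n₁ + 1/n₂).

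- 135 v 135: d = 2.802 × √(2/135) = 0.341 (exact t-test 0.342).
- 67.5 v 135: d = 2.802 × √(1/67.5 + 1/135) = 0.418 (exact t-test 0.420).

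**Step 4: power if the true requirement is another point in the range.** If n per condition gives 80% power, then d = 2.802 × √(2/n). With 135 v 135 completers, power is approximately Φ(2.802 × √(135/n) − 1.960).

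| Requirement per condition | Implied d | Power, 135 v 135 |
|---|---|---|
| 100 | 0.396 | 90% |
| 135 | 0.341 | 80% |
| 200 | 0.280 | 63% |
| 300 | 0.229 | 47% |
| 400 | 0.198 | 37% |
| 500 | 0.177 | 31% |

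Power is at least 80% for requirements up to 135 and below 80% for anything above.

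**Step 5: one intervention arm against control.** Under 1:1:2, 300 splits as 75/75/150, which is 67.5/67.5/135 after 10% loss. At d = 0.341 the standardized signal is 0.341 × √(67.5 × 135/202.5) = 0.341 × √45 = 2.287. Power is Φ(2.287 − 1.960) = 63%.

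**Step 6: group randomization.** The article gives neither an ICC nor a group size for this purpose. Assume groups of 6 to 10 and an ICC of 0.01 to 0.05. The design effect 1 + (m − 1) × ICC then runs from 1.05 to 1.45. Multiplying the exact t-test effects in Step 3 by √1.05 = 1.025 and √1.45 = 1.204 gives a detectable d of about 0.35 to 0.41 for the pooled contrast and 0.43 to 0.51 for one arm. For simplicity the same design effect is applied to both sides.

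**The case against.** Four arguments favour the plan.

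- **No printed sum is wrong.** 150 lies inside 20 to 500, 300 lies inside every implied range, and the attrition step is exact. This is true. The fault is that a unique result is presented as the consequence of inputs that do not determine it.
- **A journal article condenses.** The effect size entered in G*Power may stand in the full protocol. That would excuse an omitted detail. It does not excuse a printed derivation that fails to reach its own result, in a paragraph that also calls the size hard to determine.
- **The 0.80 belongs grammatically to the earlier studies.** That is a fair reading of the sentence. But the next sentence turns the recommendation into the number needed here, so the power claim carries over for any ordinary reader.
- **The standardized difference is not the planned metric.** This stands. The analysis section plans logistic and multinomial models, so d values describe a continuous scale only and need a counterpart for the categorical outcomes.

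A reader might also infer that the trial has about 31% power. The documents do not support that. The 31% arises only at the endpoint of 500, and only if the earlier studies' recommendation is read as an equal-arm, two-sided t-test, which the article does not say. Their outcomes also differed from this trial's. Nor does the article say that 300 was chosen because it was feasible.

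**Conclusion.** The point holds as an unsupported statement of sample size and power. The printed basis does not lead to 300. That figure matches 80% power only at an unstated d of about 0.34, with 135 completers per side, a two-sided t-test and independent participants. The pooled contrast falls short for any requirement in the cited range above 135 per condition. At the same d of 0.34, one intervention arm against control has about 63% power, given that control holds the double share. Group-level randomization lowers this further.

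The trial's actual power cannot be computed from the article, because no expected effect is given. If the true requirement is 135 per condition or less, the pooled comparison reaches 80% when participants are independent.

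**What to change.** Delete the claim that 300 follows from the range of 20 to 500 at 0.80 power. Do not put a feasibility rationale in its place unless it is true.

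Keep the total of 300 and state, for each contrast, the smallest effect detectable with 80% power after 10% loss:

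- On a continuous scale, this is at best d of about 0.34 for the intervention arms pooled against control, and about 0.42 for one arm against control.
- For the two-category outcomes in the analysis section, add the matching odds ratio or risk difference, with the control proportion assumed.
- Allow for group randomization under a stated ICC and group size. With the illustrative values in the working, the two effects become about 0.35 to 0.41 and 0.43 to 0.51.

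Reconcile the 150 per intervention condition with the 1:1:2 ratio, and say which arm holds the double share. State that a null result does not exclude effects smaller than those listed.

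The cost is a rewritten paragraph and a less favourable stated figure. No participants are added.

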### Study design

BeHealthyR is a three-arm RCT with three points in time: baseline (T0), four weeks post-baseline (T1) and twelve weeks post-baseline (T2). Between February 2018 and July 2019, a total of 300 participants will be recruited and randomized either to a stress management program (SM), stress management with a buddy program (SM-B) or a control condition (CC).

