### Randomization and blinding

Once eligibility is checked and consent is gained, participants will be randomly allocated to three conditions in a 1:1:2 allocation ratio using computer generated random numbers. For practical and logistic reasons (i.e low number of participants per group session), randomization will be done on group level (i.e potential participants attending a specific training session at a community center will be randomized to the same intervention arm). To minimize the risk of bias, randomization will be done by the principal investigator (AS) Fig. 4 shows the randomization scheme of study participants.

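### The stated 150 per intervention condition cannot be met with 300 participants in three arms at 1:1:2, so any 80% power based on it does not carry over to single-arm comparisons

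*Protocol article*

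**What the plan says.** Study design calls the trial three-arm ("BeHealthyR is a three-arm RCT with three points in time") and says that "a total of 300 participants will be recruited and randomized" to SM, SM-B or CC. Randomization and blinding fixes the split: "participants will be randomly allocated to three conditions in a 1:1:2 allocation ratio". The text does not say which arm takes the double share, and Fig. 4, which may show it, is not available here.

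Sample size calculations reports that previous studies of similar components "recommend to aim for a sample size of 20-500 participants per intervention condition", "with an alpha error of 0.05 and a power of 0.80", in order "to detect the expected effect". It then assumes 10% attrition and concludes that "an initial sample of 300 participants are needed, thus 150 in each intervention condition". No effect size, standard deviation, event rate or sidedness is given.

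The Abstract and the Aims section state the hypothesis as intervention against control. A comparison of SM-B with SM is not stated as a hypothesis.

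**The concern.** The group size in the sample size section conflicts with the design it is meant to support. The article uses the term intervention condition for SM and for SM-B separately, and sets both against the control condition. Read that way, two conditions of 150 use up all 300.

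This matters because the per-condition number is the only figure in the article from which a reader could gauge power. No effect is named. The cited range of 20 to 500 per condition corresponds to detectable standardised differences from about 0.89 down to 0.18, so it supports no particular size. A reader who takes 150 at face value will credit each intervention arm with 80% power against control when at least one arm, and probably both, has half that number. An inconclusive result for one arm could then be read as firmer evidence of no effect than it is.

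**Working it through.** **Inputs.** Total 300 (Study design; Sample size calculations). Three arms (Study design). Allocation 1:1:2 (Randomization and blinding). Attrition 10%, alpha 0.05 and power 0.80 (Sample size calculations). Two-sided testing is my assumption, as is a continuous outcome with standardised difference d and a normal approximation.

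**1. The plan's own figure.**
- Two intervention conditions of 150: 2 × 150 = 300, leaving 300 − 300 = 0 for control.
- 1:1:2: 300 × (1/4, 1/4, 2/4) = 75, 75, 150.
- Three equal arms: 300/3 = 100 each.

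The figure of 150 per intervention condition is not reproduced. It arises as 300/2, a two-group split. With control as the doubled arm, SM and SM-B pooled give 75 + 75 = 150 against 150. The attrition step fits that reading: 135/0.9 = 150 and 270/0.9 = 300.

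**2. What carries over from 150 v 150.** Suppose 150 v 150 gives exactly 80% power. Then d/SE = 1.960 + 0.842 = 2.802 for that contrast, with SE² proportional to 1/n₁ + 1/n₂. For another contrast, d/SE shrinks by the ratio of standard errors:
- 75 v 150: √[(2/150)/(1/75 + 1/150)] = √(0.01333/0.02) = 0.8165. Then 2.802 × 0.8165 − 1.960 = 0.328, and power = Φ(0.328) ≈ 62.8%.
- 75 v 75: √[(2/150)/(2/75)] = 0.7071. Then 2.802 × 0.7071 − 1.960 = 0.021, and power = Φ(0.021) ≈ 50.8%.

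Equal 10% losses in all arms cancel in these ratios, and the effect size drops out. With one-sided alpha 0.05 the figures are 65.0% and 54.5%.

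**3. Does the arm order matter?** Not to the conclusion.
- CC doubled: each intervention arm v control is 75 v 150; SM-B v SM is 75 v 75.
- SM-B doubled: SM v control is 75 v 75; the other two contrasts are 75 v 150.
- SM doubled: SM-B v control is 75 v 75; the other two are 75 v 150.

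No contrast between two single arms is ever 150 v 150.

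**4. Detectable difference at 80% power after 10% attrition** (arms 67.5, 67.5, 135), d = 2.802 × √(1/n₁ + 1/n₂):

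| Contrast as randomised | After attrition | Detectable d |
|---|---|---|
| 150 v 150 (pooled v doubled control) | 135 v 135 | 0.341 |
| 75 v 150 | 67.5 v 135 | 0.418 |
| 75 v 75 | 67.5 v 67.5 | 0.482 |

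**5. Power after attrition under assumed effects**, since the article gives none:

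| Assumed d | 150 v 150 | 75 v 150 | 75 v 75 |
|---|---|---|---|
| 0.3 | 69% | 52% | 41% |
| 0.4 | 91% | 77% | 64% |
| 0.5 | 98% | 92% | 83% |

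None of these figures allows for randomisation by group.

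**The case against.** The strongest defence is that 150 was meant as the size of each side of a pooled comparison. Both statements of the hypothesis set intervention against control, and a doubled control makes the pooled contrast 150 v 150. On that reading the sentence mislabels a group and the design itself has no shortfall. The reading is coherent and may well be what was intended. It does not rescue the sentence, because the article never says it, and under it the 80% would still cover only the pooled contrast.

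Two further objections stand and limit the point. First, the 0.80 is grammatically attached to what previous studies recommend, not to 300 or to 150 v 150. A reader might infer that single-arm comparisons are shown to have only 63% or 51% power. They are not: those values hold only if 150 per group is what 80% requires, and at d = 0.5 both contrasts would exceed 80%. Second, a reader might infer that the trial fails at its purpose of isolating the buddy's contribution. The article gives a rationale for the buddy and its own arm, but poses no SM-B versus SM hypothesis. Single arm against control is the more relevant contrast.

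The outcome analyses are planned as logistic and multinomial regression, so any figure in d is an illustration and does not describe the planned tests.

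**Conclusion.** The contradiction is certain and rests on the article's text alone: 300 participants in three arms at 1:1:2 cannot put 150 in each of SM and SM-B, whichever arm is doubled. It follows that any 80% power based on 150 per group does not carry over to single-arm contrasts. Conditional on exactly 80% at 150 v 150, two-sided 0.05 and no clustering, the figures are about 63% for 75 v 150 and 51% for 75 v 75.

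The documents do not establish what power the trial actually has for any contrast, because no effect is stated. Nor do they show that d = 0.34 was the design assumption; it is back-solved from the group size. A reader might also infer that recruitment must rise, since 150 in every arm would need 450 and 150 in each intervention arm at 1:1:2 would need 600. The documents do not support that while the pooled comparison remains a plausible intention.

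The correction is needed all the same: the trial's central sample size figure is wrong as written and can be put right by rewording.

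**What to change.** - Restate the arm sizes to agree with 1:1:2, that is 75, 75 and 150, with the sponsor confirming which arm is doubled.
- State which contrast the 80% power refers to and at what assumed effect. If it is SM and SM-B pooled against control, say so. The effect should be the one actually assumed at design; if there was none, give the d as a detectable difference.
- Add the detectable differences for single-arm contrasts as an illustration for a continuous outcome, after 10% attrition and ignoring clustering. If control is the doubled arm, these are d of about 0.34 for pooled v control, 0.42 for 75 v 150 and 0.48 for 75 v 75.
- If a design effect for group randomisation is applied, apply it to every contrast and give the ICC and group size as assumptions with a range. As an example only, group sizes of 6 to 10 and ICCs of 0.01 to 0.10 give design effects 1 + (m − 1) × ICC from 1.05 to 1.90. Multiplying by the square root (1.025 to 1.378) moves the three values to about 0.35–0.47, 0.43–0.58 and 0.49–0.66. The article gives neither input.

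The cost is one rewritten paragraph and no extra participants. The downside is that the stated power for arm-level comparisons becomes less favourable.

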### Data analysis

All statistical analyses will be performed using the Statistical Package for the Social Sciences (SPSS v21) software program. Baseline descriptive statistics will be conducted to describe the study sample using two-sided t-test for continuous variables (i.e. age at enrolment), chi-square tests or Fisher’s exact tests for categorical variables (i.e. gender, nationality, level of education). Logistic regression analysis will be performed for outcomes with two categories (i.e. good health vs bad health, high stress vs low stress, intention to quit vs no intention to quit). Multinomial regression analysis will be conducted for outcomes with more than two categories (i.e. improved, constant or deteriorating financial situation). Age, gender, and nationality will be treated as potential confounding variables. Missing data will be evaluated (depending on the amount and pattern of missingness) using different approaches. Sensitivity analyses will be done using imputation techniques for missing data to assess the robustness of the main analysis.

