### Primary outcomes

#### Depression, anxiety and stress

The Depression, Anxiety and Stress Scales (DASS-21) is a validated self-report tool consisting of three 7-item measure assessing depression, anxiety and stress over the previous week using a 4-point Likert scale ranging from 0 to 3 (never, sometimes, often and almost always) [55]. Each subscale has a possible range of scores from 0 to 21 with higher scores indicating higher levels of depression, anxiety, and stress [55]. The total scores of each subscale is summed and multiplied by two to yield equivalent scores to the full DASS-42. The DASS-21 is a reliable screening tool for symptoms of depression, anxiety and stress, has been extensively utilized in a large non-clinical population [56] and has internal consistency and concurrent validity in acceptable to excellent ranges (α for depression, anxiety and stress: 0.94, 0.87 and 0.91, respectively) [57].

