#### Financial health

To measure financial health, participants will be asked to report: 1) their total monthly income (< 1750€, 1750-2750€, > 2750€, don’t want to report); 2) whether they receive welfare (yes, no); 3) their spouse/partner’s total monthly income (don’t have any partner, < 1750€, 1750-2750€, > 2750€, don’t want to report, I don’t know); and 3) whether they have experienced money shortages in the past month (1 = never, 2 = sometimes, 3 = frequently, 4 = often and 5 = almost always). The proportion of participants in each category for each question asked will be calculated.

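### The named outcome models cut stress and general health to two classes and ignore the order of the financial classes, which costs power on three primary outcomes

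*Protocol article*

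**What the plan says.** The Data analysis section of the protocol article assigns models to outcomes by number of categories. For two classes: "Logistic regression analysis will be performed for outcomes with two categories (i.e. good health vs bad health, high stress vs low stress". For three: "Multinomial regression analysis will be conducted for outcomes with more than two categories (i.e. improved, constant or deteriorating financial situation". The covariates it names are age, gender and nationality. The t-test it mentions is for baseline description.

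The outcome sections describe finer data:

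- **Stress** is a seven-item subscale scored 0 to 21 and then rescaled: "The total scores of each subscale is summed and multiplied by two to yield equivalent scores to the full DASS-42".
- **General health** is one item with five ordered levels, from poor to excellent.
- **Financial health** includes a five-level ordered item on "whether they have experienced money shortages in the past month", plus income bands and welfare status.

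All three stand under Primary outcomes. Study design sets T0, T1 and T2 as the measurement points, and the Control group section has controls complete the questionnaires at the same three times.

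**The concern.** A split of an ordered score treats everyone on one side of the cut as alike. A participant whose stress falls a long way without crossing the cut counts as no change. One who moves a single point across it counts as a full success. No cut-point for stress or health is given. The three financial classes run from better to worse, but multinomial regression fits them as if they had no order, so it spends two degrees of freedom per arm contrast where one would do.

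For stress and health, the T0 value of the outcome is normally the strongest available predictor of the later value, yet it is not among the named covariates. At stake is power on three primary outcomes, in a trial whose size is fixed at 300 without a stated effect size.

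**Working it through.** **Inputs from the article**

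- Error rates: "with an alpha error of 0.05 and a power of 0.80. to detect the expected effect". Two-sided testing is assumed.
- Size: "Assuming expected attrition of 10%, an initial sample of 300 participants are needed, thus 150 in each intervention condition".
- Effect size: none. The section offers only a range ("recommend to aim for a sample size of 20-500 participants per intervention condition").
- Allocation: "participants will be randomly allocated to three conditions in a 1:1:2 allocation ratio using computer generated random numbers", that is 75/75/150 of 300.

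**Assumed, because the article does not give them:** score distributions, cut-points, the T0-to-T2 correlation r, and no clustering.

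**Step 1. The plan's own figure.** 300 × 0.90 = 270, and 270/0.90 = 300, so the attrition step is consistent. The 270 itself cannot be re-derived without an effect size. Under 1:1:2, the only comparison of 150 v 150 is both intervention arms pooled against control, or 135 v 135 after attrition. Solving backwards for 80% power:

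d = (1.960 + 0.842) × √(2/135) = 0.341.

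This d is an anchor, not a planned effect. For one intervention arm v control (67.5 v 135), the detectable d is 2.802 × √(1/67.5 + 1/135) = 0.42.

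**Step 2. Splitting stress.** For a normal score, the information kept by a split with proportion p on one side is E = φ(z)²/[p(1 − p)]. Power is Φ(2.802√E − 1.960).

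| Split | E | Loss | Power from E |
|---|---|---|---|
| none | 1 | 0% | 80% |
| 50/50 | 0.1592/0.25 = 0.637 | 36% | 61% |
| 30/70 | 0.1209/0.21 = 0.576 | 42% | 57% |
| 20/80 | 0.0784/0.16 = 0.490 | 51% | – |

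A direct two-proportion calculation at d = 0.342, with 50%, 30% and 20% of controls in the high class, gives power of 60%, 53% and 45%. The number per group needed for 80% rises from 135 to 215, 255 and 314.

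The result depends on the distribution. With 22 equally used levels under proportional odds, the full score carries (1 − Σp³)/3 = (1 − 1/484)/3 = 0.333 and a median split carries 0.25, a loss of 25%.

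**Step 3. Splitting general health.** The same comparison, p(1 − p) against (1 − Σp³)/3, for assumed five-level distributions:

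| Level proportions | Cut at | Kept | Loss |
|---|---|---|---|
| 0.2 each | 0.4 | 0.24/0.320 | 25% |
| 0.2, 0.4, 0.3, 0.08, 0.02 | 0.6 | 0.24/0.300 | 20% |
| 0.3, 0.4, 0.2, 0.08, 0.02 | 0.3 or 0.7 | 0.21/0.300 | 30% |
| 0.1, 0.25, 0.4, 0.2, 0.05 | 0.75 | 0.1875/0.304 | 38% |

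The first three are central cuts. The last is off-centre.

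**Step 4. Adjusting continuous stress for T0.** The variance is multiplied by 1 − r², so power is Φ(2.802/√(1 − r²) − 1.960): 84% at r = 0.3, 90% at r = 0.5 and 94% at r = 0.6.

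**Step 5. Ignoring order in the financial classes.** A one-degree-of-freedom test with 80% power has noncentrality 7.849. A two-degree-of-freedom test needs 9.635. The ratio is 7.849/9.635 = 0.815, a 19% loss, and the two-degree test at 7.849 has 71% power. This assumes the effect runs along the order of the classes.

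A simulation (4,000 runs per scenario, 135 v 135, latent normal five-level item, r = 0.4 or 0.6, simple tests standing in for the regressions) agrees. The three-class change outcome had power of 45 to 65% with order ignored and 56 to 75% with order used, a gap of about 10 points in each scenario. The baseline-adjusted five-level item reached 80 to 89%. That last contrast also reflects coarser classes and a different use of T0, so it is not the cost of ignoring order alone.

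**The case against.** The best defence is that this is a condensed article. It introduces the outcomes with i.e., which it uses elsewhere to give examples, and it says which model suits which kind of outcome, not that no other analysis will be run. It defines a total DASS-21 score, and the pilot summarised stress as a mean. A continuous or baseline-adjusted analysis in an unseen analysis plan is therefore not excluded. That stands, and the point is limited accordingly. But the outcomes the article chose to name are its own primary outcomes, expressly tied to these models. An added analysis would conflict with that text.

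The defence is also right that the sizes rest on assumptions. The power figures ignore randomisation by group and fit only the pooled comparison. With clustering, the absolute powers would be lower.

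A reader might infer more than the text supports:

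- **That every primary outcome is affected.** Data analysis splits no smoking quantity. Its one smoking example, intention to quit, is naturally binary, and the 10 ppm carbon monoxide cut-off defines a binary status.
- **That models for cigarettes per day, FTND or carbon monoxide level are missing.** A condensed article may leave these to the full plan.
- **That finances ignore baseline.** Improved, constant or deteriorating is already relative to an earlier value. The fault there is coarse classes with order ignored.
- **That at least a third of the information is always lost.** Steps 2 and 3 show losses of 20 to 30% in plausible cases.
- **That participants will stay in the high-stress class because they enrol stressed.** Entry requires perceived stress, with no DASS threshold, and the high/low cut is not given.

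**Conclusion.** The concern holds in limited form. For stress and general health, the article names two-class models that discard information already collected. For finances, it names a model that ignores the order of the classes. For stress and health, the T0 value is not among the named covariates.

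The split alone loses roughly 20 to 50%, depending on cut-point and distribution. Under the Step 1 anchor, the cost for stress is about 19 points of power at a median split (80% to 61%). A continuous analysis with T0 adjustment would instead gain about 4 to 14 points (to 84 to 94%). For finances, ignoring order alone costs about 9 points (80% to 71%). These powers are illustrations of relative cost, not forecasts for this trial.

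The weakness reduces efficiency and leaves cut-points open. It does not invalidate the comparison between arms. The analysis should be changed, but the trial does not depend on it.

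**What to change.** Amend the Data analysis section as follows.

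- **Stress:** analyse the DASS-21 stress score as continuous, in a linear mixed model of T1 and T2 with arm, time, arm by time and the T0 score.
- **General health and the money-shortage item:** ordinal (proportional-odds) models at T2, adjusted for the T0 level.
- **All three:** include a term for the randomised group, and name the arm contrasts (for example each intervention arm v control, or pooled v control), since there are three arms.
- **Category tables:** keep high/low stress, good/bad health and the three financial change classes as descriptive or supportive results. Fix their cut-points before the data are seen.
- **Income and welfare status:** leave these as reported financial measures. Nothing here requires redefining the financial outcome.

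The cost is a change of analysis wording. The questionnaires are already planned at T0, T1 and T2, so no new data are needed. The small downside is that results appear as mean differences or common odds ratios instead of simple proportions, which the supportive tables largely make good.
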